**Figure 3 F3:**
[figure not shown]
**Flowchart HOMERUS study**.

#### Functional capacity of the affected upper limb

The DASH score will be used to determine functional capacity [30,31]. This questionnaire consists of 30 questions about symptoms and function of the upper limbs that are affected by disorders of the musculoskeletal system. It provides a single main score, the DASH function/symptom score, which is a summation of the responses on a scale of 0 (no disability) to 100 (severe disability). The degree of difficulty in performing a variety of daily physical activities because of arm, shoulder or hand problems is determined (21 items), as well as the severity of pain, activity-related pain, tingling, weakness and stiffness (5 items), and the effect of the upper-limb problems on social activities, work, sleep and self-image (4 items).

#### Pain

The amount of experienced pain is measured on a 10-point Visual Analogue Scale (VAS), from no pain (0) to most extreme pain imaginable (10).

#### Patient satisfaction

The amount of experienced satisfaction with the result of surgical treatment is measured on a 10-point Visual Analogue Scale, from no satisfaction at all (0) to complete satisfaction (10).

#### Shoulder function

Functional outcome is measured with the Constant-Murley score. This score system combines shoulder function tests (65 points) with a subjective evaluation of the patients (35 points) [32].

#### Quality of life

Health-related quality of life is measured with the Short-Form 36 (SF-36) score. This is a validated multi-purpose, short-form health survey with 36 questions, representing eight health domains [33,34].

#### Radiological evaluation

Standard X-rays (40° posterior oblique view with external rotation of the humerus, 40° posterior oblique view with internal rotation of the humerus, and an axillary view) and computer tomography will be taken preoperatively and used for classification of fracture type and surgery-planning purposes. Postoperative imaging will consist solely of standard X-rays. Points of particular interest in hemiarthroplasty are signs of loosening; periarticular calcification; displacement, dislocation or necrosis of the tuberosities; glenohumeral subluxation; periprosthetic lucency; component shift; loss of glenoid cartilage; and presence of bony erosion on the glenoid. In angle-stable locking compression plate osteosynthesis axial and rotational deformities of the head fragment and/or greater tuberosity fragment after surgery will be assessed radiographically according to Bahrs et al. [35]. Secondary displacement of the fracture, screw perforation, humeral head necrosis classified according to Cruess [36], plate impingement and delayed fracture healing/pseudoarthrosis will also be recorded.

#### Complications

All complications will be recorded during the study period.

#### Sample size

Different studies on clinical outcomes following hemiarthroplasty in the treatment of three- and four-part fractures of the proximal humerus state that the DASH score is about 40 [37,38]. Sample size calculation was performed; primary outcome measure was the DASH score, whereby 10 points after 24 months was considered a clinically relevant difference between the two groups, with a standard deviation of 19.4, alpha set on 5% and power on 80%. This resulted in a required number of 61 patients in each group. Assuming a dropout rate of 10%, two groups of 67 patients will have to be included.

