**Methods/Design:**

A randomized controlled multicenter trial will be conducted. Patients older than 60 years of age with a dislocated three- or four-part fracture of the proximal humerus as diagnosed by X-rays and CT-scans will be included. Exclusion criteria are a fracture older than 14 days, multiple comorbidity, multitrauma, a pathological fracture, previous surgery on the injured shoulder, severely deranged function caused by a previous disease, "head-split" proximal humerus fracture and unwillingness or inability to follow instructions. Participants will be randomized between surgical treatment with hemiarthroplasty and angle-stable locking compression plate osteosynthesis. Measurements will take place preoperatively and 3 months, 6 months, 9 months, 12 months and 24 months postoperatively. Primary outcome measure is speed of recovery of functional capacity of the affected upper limb using the Disabilities of Arm, Shoulder and Hand score (DASH). Secondary outcome measures are pain, patient satisfaction, shoulder function, quality of life, radiological evaluation and complications. Data will be analyzed on an intention-to-treat basis, using univariate and multivariate analyses.

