### Measurements

Outcome assessment will take place in both groups at randomization (T0), 3 months postoperatively (T1), and 6, 9, 12 and 24 months (T2, T3, T4, T5) postoperatively. Outcome assessment for T0, T1, T4 and T5 will take place in an outpatient clinic setting and involves all outcome measures. At six and nine months postoperatively (T2 and T3) patients will only fill in a questionnaire that will be sent and returned by mail [Figure 3]. Speed of recovery of functional capacity of the affected upper limb is our primary outcome measure. Secondary outcome measures are pain, patient satisfaction, shoulder function, quality of life, radiological evaluation and complications.

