### Statistical analysis

To estimate the effect of the interventions, analyses will be performed using the Statistical Package for the Social sciences (SPSS) 19.0. The baseline characteristics from both study groups will be compared for equality by means of an independent samples T-test for continuous variables and a chi-square test for dichotomous variables. Random effect models will be applied for longitudinal analyses. A p-value lower than 0.05 will be considered as statistically significant. Data will be analyzed according to the intention-to-treat principle and the research data will be reported following the CONsolidated Standards of Reporting Trial (CONSORT).

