## Discussion

Both hemiarthroplasty and angle-stable locking compression plate osteosynthesis for dislocated three-and four-part fractures of the proximal humerus in the elderly are performed in current practice. The optimal surgical management remains controversial and a clear distinction between indications for one of both treatment options cannot be made on the basis of the current evidence in the literature. To date, there are no randomized controlled studies that compare the outcome of hemiarthroplasty vs. angle-stable locking compression plate osteosynthesis in the treatment of dislocated three- and four-part fractures of the proximal humerus. The HOMERUS study is designed to determine which treatment results in better outcome, defined as speed of recovery of functional outcome. Further, it is possible to identify which treatment will provide better outcomes in pain, satisfaction, shoulder function, quality of life, radiological evaluation and complications.

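### The primary outcome is speed of recovery, but the sample size and its 80% power are for a 10-point DASH difference at 24 months

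*Protocol article*

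**What the plan says.** Three places in the protocol article agree on the primary outcome. The Methods/Design paragraph of the Abstract says "Primary outcome measure is speed of recovery of functional capacity of the affected upper limb", measured with the DASH. Measurements says "Speed of recovery of functional capacity of the affected upper limb is our primary outcome measure". The Discussion describes the trial as "designed to determine which treatment results in better outcome, defined as speed of recovery of functional outcome". The Discussion paragraph of the Abstract likewise promises to show which operation gives the quickest return of function.

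The Sample size section names something else: "primary outcome measure was the DASH score, whereby 10 points after 24 months was considered a clinically relevant difference between the two groups". The calculation there takes an SD of 19.4, a 5% alpha and 80% power and arrives at 61 patients per group, raised to 67 for dropout.

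DASH is collected at randomization and at 3, 6, 9, 12 and 24 months. On repeated measurements, the Statistical analysis section says "Random effect models will be applied for longitudinal analyses" and goes no further.

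**The concern.** Both statements use the same questionnaire, so they can look consistent. They concern different quantities. The final score describes where patients end up; speed describes how soon they get there. One arm can be well ahead at 3 and 6 months and level at 24. Two arms can also run together through the first year and separate later.

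The primary outcome decides what the trial may conclude. As written, the 80% power is attached to a question that three sections do not call primary, and the question they do call primary has no target difference, variance or power. If the early and final results disagree, either could be presented as the primary result with support from the text.

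**Working it through.** **Inputs from the Sample size section.** Difference δ = 10 DASH points at 24 months, SD σ = 19.4, alpha 5%, power 80%, equal groups. Sidedness is not stated; two-sided is assumed.

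**Step 1: reproduce the plan's figure.**
- Normal approximation: n = 2(z₀.₉₇₅ + z₀.₈₀)²σ²/δ² = 2 × (1.960 + 0.842)² × 19.4² / 10² = 59.08, so 60 per group.
- t-test with standardised difference 10/19.4 = 0.515: n = 60.06, so 61 per group. This is the plan's number.
- A one-sided normal calculation gives 47 and does not match.
- Power of the two-sided t-test at 61 per group is 80.6%.

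The arithmetic is sound. It is a comparison of two means at one visit. Nothing in it describes change over time: it has no within-patient correlation, no earlier visit and no time to a threshold.

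**Step 2: what that comparison detects when speed differs but the end level is similar.** Same t-test, 61 per group, SD 19.4. The remaining differences are assumed.

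| True difference at 24 months | Power |
|---|---|
| 10 points | 80.6% |
| 3 points | 13.5% |
| 2 points | 8.7% |
| 0 points | 5% (alpha only) |

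**Step 3: illustrate one possible speed contrast.** Take the between-group difference in mean DASH over 3, 6, 9 and 12 months. Assume SD 19.4 at each visit and the same correlation ρ between any two visits; the article gives neither. Then SD of the four-visit mean = 19.4 × √((1 + 3ρ)/4).

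Two average differences are tried. One is 10 points, which the article justifies only for 24 months. The other comes from an assumed gap that closes over the year, of 12, 8, 4 and 1 points at the four visits: (12 + 8 + 4 + 1)/4 = 6.25.

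| ρ (assumed) | SD of mean | Power, 10 points | Power, 6.25 points |
|---|---|---|---|
| 0.5 | 15.34 | 94.7% | 60.7% |
| 0.6 | 16.23 | 92.1% | 55.9% |
| 0.7 | 17.08 | 89.4% | 51.8% |
| 0.8 | 17.89 | 86.5% | 48.2% |

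For 6.25 points, 80% power would need about 96 (ρ = 0.5) to 130 (ρ = 0.8) evaluable patients per group. Power for speed thus lies on either side of 80%, depending on the contrast, the target difference and the correlation.

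**The case against.** The best defence is that this is a condensed article. A full protocol or analysis plan, not shown, may say which parameter of the random effects model expresses speed, and such detail normally belongs there. That stands, so the missing definition is not counted as a fault in itself. It does not remove the contradiction: the article names one primary quantity in three sections and a different one in the Sample size section. A definition elsewhere would not make a 24-month calculation apply to speed.

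A second defence is that the longitudinal model uses all visits, so the trial may have adequate power for speed. That is possible, and the working does not rule it out.

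Three stronger readings are tempting and are not supported:
- **That the trial is underpowered for speed.** This cannot be shown, because no speed effect is specified. The 14% and 5% figures concern the 24-month comparison under assumed small differences, not the power for speed.
- **That speed will be analysed as a straight-line slope over 0 to 24 months**, which the last visit would dominate and which could rank the arms wrongly. The Statistical analysis section names random effects models only. A model with visit as a categorical factor fits that wording equally well.
- **That DASH will be tested separately at five visits with an inflated error rate.** No such testing is planned in the text.

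It can also be objected that mean DASH over 3 to 12 months is itself an average level: two curves a constant distance apart from 3 months onward would differ on it. That is fair. It is one workable summary of early recovery, offered as an example.

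**Conclusion.** The point holds as an internal contradiction. The 61 per group and 80% power belong to a 10-point DASH difference at 24 months (80.6% by two-sided t-test), while the stated primary outcome is speed of recovery, for which no power is given. This rests on the article's own text and figures plus a two-sided test, which reproduces the stated number. The size of any shortfall for speed is unknown. The 48% to 95% range in the working depends on assumed correlations, a constant SD and assumed average differences, and serves only to show that the 80% cannot be carried over.

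**What to change.** Make the primary outcome and the sample size refer to the same quantity, by one of two routes.

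**(a) 24-month DASH as primary.** Name DASH at 24 months as the primary outcome in the Abstract, Measurements and Discussion. Keep the calculation, remove speed and quickest-recovery wording from the primary conclusion, and report the earlier course as secondary. Cost: wording, including the registry entry if it says the same. Patients and visits are unchanged.

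**(b) Speed as primary.** Define speed as one measurable contrast on the early DASH visits. An example is the between-group difference in mean DASH over 3 to 12 months, from the random effects model with visit as a categorical factor. Justify a relevant difference for that contrast, since 10 points is argued only for 24 months. Restate the power at 61 per group as a range over plausible between-visit correlations, and make 24-month DASH secondary. Cost: a new sample-size paragraph and no extra visits. The downside is that the restated power may fall below 80%, in which case the sponsor must either accept that openly or recruit more patients.

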### Statistical analysis

To estimate the effect of the interventions, analyses will be performed using the Statistical Package for the Social sciences (SPSS) 19.0. The baseline characteristics from both study groups will be compared for equality by means of an independent samples T-test for continuous variables and a chi-square test for dichotomous variables. Random effect models will be applied for longitudinal analyses. A p-value lower than 0.05 will be considered as statistically significant. Data will be analyzed according to the intention-to-treat principle and the research data will be reported following the CONsolidated Standards of Reporting Trial (CONSORT).

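### Baseline significance tests for equality are uninformative in this randomised trial; describe baseline instead and fix hospital, age and fracture type as model terms in advance

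*Protocol article*

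**What the plan says.** The Statistical analysis section sets out the baseline comparison: "The baseline characteristics from both study groups will be compared for equality by means of an independent samples T-test for continuous variables". Two-category characteristics are to be compared by chi-square instead. The only threshold given is general: "A p-value lower than 0.05 will be considered as statistically significant". The article does not say what follows from a significant or a non-significant baseline result.

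For outcomes the same section says "Random effect models will be applied for longitudinal analyses" and names no covariates. The abstract adds: "Data will be analyzed on an intention-to-treat basis, using univariate and multivariate analyses". Some multivariable analysis is therefore announced, but its terms are not given.

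Three pre-treatment facts are available according to the article:
- **Hospital.** Under Study design, each hospital has its own allocation sequence, in blocks of ten.
- **Age.** It is an eligibility criterion (Study population).
- **Fracture type.** Under Radiological evaluation, X-rays and CT "will be taken preoperatively and used for classification of fracture type and surgery-planning purposes". CT also precedes inclusion, because the displacement criterion is read from it (Study population).

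**The concern.** A significance test asks whether an observed difference could be due to chance. When allocation is random, the answer is already known: it is. A baseline test of equality can then mislead in two ways. A non-significant result may be read as showing balance, although with this sample size sizeable gaps are not significant. A significant result may be read as a real inequality, although some are expected by chance when many variables are tested.

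What matters for the treatment comparison is how large a gap is and how strongly the variable predicts DASH. The p-value of the gap measures neither of these combined. If the tests appear in the report and the model terms are not fixed, the analyst is left free to react to the baseline table. An adjustment that is fixed in advance removes that freedom. It also corrects for whatever chance imbalance occurs, and usually narrows the confidence interval.

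**Working it through.** **1. The plan's own sample size.** Inputs from Sample size: "10 points after 24 months was considered a clinically relevant difference between the two groups", SD 19.4, alpha 5%, power 80%.

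Normal formula: n = 2 × (1.96 + 0.84)² × 19.4² / 10² ≈ 59.1, so 60 per group. The t-distribution version gives 60.06, rounded up to 61, which is the stated figure. With 10% added, 61 × 1.10 = 67.1, close to the stated 67. This is an unadjusted two-group comparison, so the planned power does not depend on adjustment.

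**2. Smallest gap that a baseline test would flag, 67 per group.**
- Continuous variable: 1.96 × √(2/67) = 0.339 SD (0.342 with the t critical value).
- Dichotomous variable: 1.96 × √(2p(1−p)/67). At p = 0.25 this is 14.7 points; at p = 0.50 it is 16.9 points. The prevalences are assumed.

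**3. How often relevant gaps occur by chance.** At 50% prevalence the standard error of the difference is √(2 × 0.25/67) = 0.0864. A gap above 10 points has probability 24.7% (0.10/0.0864 = 1.16). Since 5% of gaps exceed the flagging limit, about 20% of such trials would have a gap between 10 and 17 points and be called equal. A gap of 15 points has p = 0.082 and would also pass.

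**4. Spurious differences.** With k independent tests at 5%, the chance of at least one significant result is 1 − 0.95^k: 23% for five, 34% for eight, 40% for ten. The number of baseline variables is not stated, and independence is assumed.

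**5. What a passed gap could do to an unadjusted comparison.** Shift in DASH = gap (in SD) × rho × 19.4, where rho is the covariate's correlation with DASH. The documents give no rho, so a range is assumed. Conditional type I error is computed with 61 per group, using the critical value 1.96 × √(2/61) and conditional standard error √((1−rho²) × 2/61), both in SD units.

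| Gap | rho | Shift in DASH points | Conditional type I error |
|---|---|---|---|
| 0.20 SD | 0.3 | 1.2 | 5.2% |
| 0.20 SD | 0.5 | 1.9 | 5.4% |
| 0.30 SD | 0.3 | 1.7 | 6.8% |
| 0.30 SD | 0.5 | 2.9 | 9.6% |

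The target difference is 10 points. A gap of 0.20 SD corresponds to 10 points on a 50% factor, and 0.30 SD to 15 points.

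**6. What adjustment would gain.** Residual SD = 19.4 × √(1−rho²), with rho now the multiple correlation of the covariate set with DASH at 24 months. Power = Φ(10 / (residual SD × √(2/61)) − 1.96).

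| rho (assumed) | Residual SD | Power, 61 per group | n per group for 80% |
|---|---|---|---|
| 0 | 19.4 | 81.2% | 60 |
| 0.2 | 19.0 | 82.8% | 57 |
| 0.3 | 18.5 | 84.7% | 54 |
| 0.4 | 17.8 | 87.4% | 50 |
| 0.5 | 16.8 | 90.8% | 45 |

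These figures apply to the 24-month contrast used for sizing, by the normal formula.

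**The case against.** The strongest reply is that the sentence may describe no more than a baseline table. It ties the tests to no decision, so on its own it changes neither the primary estimate nor its error rate nor its power. That stands.

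A reader might infer four stronger things that the article does not support:
- **That the tests choose the covariates.** No such rule is stated. The text leaves this open, and no more can be said.
- **That the lack of a covariate list is an error.** The abstract announces multivariable analysis. A condensed article commonly leaves the list to a full protocol or analysis plan, neither of which is shown.
- **That the treatment estimate is biased.** Under correct randomisation the unadjusted estimate is unbiased over repeated allocations. The shifts in step 5 are conditional on a particular chance gap. The larger ones need a gap close to the flagging limit.
- **That age and fracture type are known predictors of DASH.** The Background lists factors associated with poor outcome, and these two are not among them. Their prognostic strength, and so the gain in precision, is an assumption. At rho 0.2 the gain is under two percentage points of power.

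One could also defend baseline tests as a check that allocation was not subverted. The article gives no such purpose, and its wording concerns equality of the groups.

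None of this rescues the tests. They are a stated procedure, not an omission, and a fuller plan that added a covariate list would still need to drop or reinterpret this sentence.

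**Conclusion.** The point holds in a limited form. The planned baseline tests are uninformative in a randomised trial. With 67 per group they would call equal any gap below about 0.34 SD, or about 15 to 17 percentage points at 25 to 50% prevalence (assumed). Ten independent tests would produce at least one spurious difference about 40% of the time. The stated sample size and power are valid for an unadjusted comparison and are not in question.

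The remaining concern is conditional imbalance, analyst discretion and efficiency. Its size depends on correlations that the documents do not give: with rho 0.2 to 0.5 assumed, adjustment moves power from about 81% to between 83% and 91%. Severity is minor to moderate.

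**What to change.** 1. Delete the baseline t-tests and chi-square tests. Report baseline by group with means and SDs (or medians and quartiles), counts and percentages, without p-values.
2. State that the random effects model for DASH includes hospital, age and three- versus four-part fracture on CT, whatever balance is observed. Hospital belongs there because patients are randomised within it. Use the fracture type recorded at eligibility, so that the classification cannot be influenced by allocation.
3. State that these terms are fixed before outcome data are seen and are never chosen by baseline p-values.
4. Report the unadjusted estimate alongside the adjusted one.

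The cost is a few sentences of analysis text. No patients, visits or measurements are added, since the article already has hospital, age and CT classification available before surgery. The sample size can stay as it is. If a full protocol or analysis plan already fixes covariates, only the first item and a check for consistency are needed.

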## Discussion

Both hemiarthroplasty and angle-stable locking compression plate osteosynthesis for dislocated three-and four-part fractures of the proximal humerus in the elderly are performed in current practice. The optimal surgical management remains controversial and a clear distinction between indications for one of both treatment options cannot be made on the basis of the current evidence in the literature. To date, there are no randomized controlled studies that compare the outcome of hemiarthroplasty vs. angle-stable locking compression plate osteosynthesis in the treatment of dislocated three- and four-part fractures of the proximal humerus. The HOMERUS study is designed to determine which treatment results in better outcome, defined as speed of recovery of functional outcome. Further, it is possible to identify which treatment will provide better outcomes in pain, satisfaction, shoulder function, quality of life, radiological evaluation and complications.
